#### Sample size

With a sample size of 150, we will be able to estimate the proportion of participants who are hypothetically willing and eligible to be randomised in a clinical study to within a 95% CI of ±7%. We also wish to identify the case mix of patients for each of the possible treatment options. From our patient survey, the least favourable treatment option was minor surgical operations, (13%), which would include deroofing of skin tunnels. One hundred and fifty patients will provide us with 20 patients opting for this non-medical intervention, which is sufficient to explore delivery in the IDEAL 2b evaluation.

### Recruitment

The study team will work closely with the UK Dermatology Clinical Trials Network to publicise the study, provide study updates, facilitate the recruitment of additional sites, if needed while keeping current sites updated on recruitment progress against our target sample size.

The Cardiff Centre for Trials Research (CTR) study team will be in close contact with all recruiting sites, providing a regular newsletter highlighting current recruitment rates, any changes to the recruitment period and other issues that sites need to be aware of.

### Data collection and management

#### Plans for assessment and collection of outcomes

##### Baseline data collection

The THESEUS study will use a bespoke Structured Query Language (SQL) database for data capture. During the baseline appointment the clinician will capture data, as outlined in the schedule of interventions and assessments (table 1), using the baseline case report form, (CRF). Current medical management of their HS will be recorded, including any concomitant medications and interventions received in the last 12 months. The clinician will record the participants’ clinical examination findings, (regions of the body affected by HS, number of inflammatory lesions and the presence and extent of skin tunnels) and determine their Hurley stage^14^ for each region.

**Table 1 T1:** Schedule of interventions and assessments

Review number	−1	0	1	2	3	4
Planned month	−1	Baseline	3	6	9	12
Screening logs	X	X				
Eligibility assessment	X	X				
Demographics and consent		X				
Clinical examination including Hurley stage*		X	X	X	X	X
Interventions for which participant is potentially eligible		X				
Intervention received, with reasons for choice (including treatments switched after baseline)		X	X	X	X	X

##### Follow-up data collection

Follow-up reviews will be conducted over the telephone or at the outpatient clinic in person at 3 months, 6 months, 9 months and up to 12 months after the baseline appointment. The option for remote telephone follow-up was introduced via a protocol amendment, due to the COVID-19 pandemic and the subsequent restrictions on face-to-face appointments. Follow-up reviews are not anchored to treatment schedules and are conducted regardless of whether the participant has received their THESEUS intervention yet.

The clinical examination will be repeated at each follow-up review and recorded by the clinician. The measures completed at the baseline appointment, with the addition of a change in disease severity anchor measure, will be completed by the participant at each follow-up review.

The clinician will document which treatments or procedures the participant has received at each follow-up review using the intervention CRF. Clinicians will use this CRF to record intervention choice changes and any additions to the participant’s treatment regimen. An adverse event notification CRF is available at each review should the participant report any study-related adverse effects.

##### Pain score text messages

The THESEUS study is testing the feasibility of collecting participants’ daily pain NRS scores via short message service text messages. The text messages are triggered by the addition of specific data items, (depending on the chosen intervention) being added into the baseline intervention CRF within the SQL database.

The text messages are sent by Esendex; a telecommunications service provider. This is an automated process whereby Esendex is instructed to send the same message to the participant asking about the participant’s current pain magnitude due to their HS, daily for up to 12 weeks from the day the intervention was commenced. The text message is sent to the participants at the same time each day, (06:00). The participant has until 02:00 the following day to respond to provide their pain score for that day.

Participants are sent the following text message:

‘Hello. This a text message from the THESEUS study. Please indicate the level of pain you are CURRENTLY experiencing due to your HS. The scale is from 0 to 10. ‘0’ means no pain and ‘10’ means pain as severe as it could be. You have until 02.00 am tomorrow morning to return today’s pain score. If you no longer wish to receive these messages, please text STOP to [THESEUS telephone number].’ ‘Copyright of Cardiff University and HISTORIC.’

##### Nested qualitative studies

###### Study 1

On each occasion where conventional surgery, deroofing or laser intervention is used, the operator will be asked to complete a questionnaire which details the technique used, duration of procedure, adaptations to the procedure and resources used. Up to three centres will be purposefully sampled to video record a small sample of laser and surgical procedures to help document variation in practice and produce materials demonstrating best practice.

###### Study 2

A subset of study participants (approximately 50 participants) who agree to take part in a telephone interview will be asked about their experiences of taking part in THESEUS. This will include factors influencing their choice of intervention and facilitators and obstacles to taking part in HS clinical trials. Purposive sampling of cohort participants will ensure a spread of procedural interventions, (conventional surgery, deroofing and laser treatments) and those opting for drug treatments. Sampling will also ensure diversity in age, gender, ethnicity, HS severity and geographical location. Interviews with at least one clinician at each recruiting site will also be undertaken to receive feedback on taking part in THESEUS from a healthcare professional/researcher perspective.

###### Study 3

All cohort participants and recruiting clinicians will be asked to complete an end of study questionnaire, covering satisfaction with treatments, barriers to and facilitators for participating in HS research, in addition to influences on treatment choice.

##### End of study consensus workshop

The study results will be used to inform a series of multistakeholder workshops, conducted both virtually and face-to-face. The workshop will consider the design and interventions to include in future HS RCTs.

#### Plans to promote participant retention and complete follow-up

The severity of the COVID-19 pandemic in the UK in March 2020, resulted in a national lockdown. Face-to-face appointments for patients became difficult; as a result, the option for remote recruitment and remote follow-ups was implemented in order to improve recruitment and follow-up rates. For participants where remote recruitment or remote follow-up is appropriate, patients have the option of: self-reporting their lesions, providing the site with still photographs, or taking part in a remote video consultation for a clinician to assess their lesions. Video consultations involving assessment of intimate skin regions will be conducted with a chaperone present using a secure NHS approved digital interface.

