### Who will take informed consent?

Consent will be taken by suitably qualified Principle Investigators (PIs), coinvestigators and research nurses. The recruitment appointment will be carried out face–face for patients who are not known to the recruiter. However, for those patients who are already known to the study team, eligibility, consent and the baseline appointment can be performed remotely, if necessary, without the need for the patient to attend the hospital clinic. The option for remote recruitment was introduced via a protocol amendment as a result of the COVID-19 pandemic.

The consent form will have an option to approve being contacted about taking part in a study interview or joining an end-of-study consensus workshop. Prior to the interview, consent will be taken over the telephone by a study researcher; this process will be audio recorded. Participants who agree to attend the consensus workshop will not be asked formally for their consent, as their attendance will provide implied consent.

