### Outcomes

Primary outcomes measure(s):

Proportion of participants who are eligible, and hypothetically willing, to use the different treatment options at baseline.

Secondary outcomes measure(s):

Proportion of participants choosing each of the study interventions, with reasons for their choices.Proportion of participants who switch treatments within the first 6 months of treatment, with reasons for switch.Treatment fidelity over 6 months.Loss to follow-up rates over 12 months.Efficacy outcome estimates after 6 months of follow-up to contribute to OMI validation and to inform the end-of-study workshop regarding future RCT designs. Instruments include: lesion counts, HS Quality of Life Questionnaire (HiSQOL), Dermatology Life Quality Index (DLQI), Pain Numerical Rating Scale (NRS), Fatigue Questionnaire, Patient Global Assessment.

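### Lesion counts may come from clinic, video, photographs or self-report, but the stated change and ROC/MID analyses do not separate these modes

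*Protocol article*

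**What the plan says.** **Baseline.** Under Baseline data collection, the clinician records the examination findings, including "number of inflammatory lesions and the presence and extent of skin tunnels". Under Who will take informed consent?, "The recruitment appointment will be carried out face–face for patients who are not known to the recruiter"; for patients already known to the study team, "eligibility, consent and the baseline appointment can be performed remotely, if necessary".

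**Follow-up.** Under Follow-up data collection, "Follow-up reviews will be conducted over the telephone or at the outpatient clinic in person", and the same section adds: "The clinical examination will be repeated at each follow-up review and recorded by the clinician". Plans to promote participant retention and complete follow-up then sets out what happens when recruitment or follow-up is remote: "patients have the option of: self-reporting their lesions, providing the site with still photographs, or taking part in a remote video consultation". Of these three routes, only the video consultation is expressly for a clinician to assess the lesions.

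**Use of the counts.** Under Outcomes, lesion counts are the first instrument listed for "Efficacy outcome estimates after 6 months of follow-up to contribute to OMI validation".

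**Analysis.** Statistical methods for primary and secondary outcomes plans one estimate of change from baseline to 6 months, with a 95% CI, for each efficacy outcome in each group, plus a general statement that potential confounders will be examined by regression. For validation, a global assessment is the anchor. It splits participants into those with and without meaningful change; ROC curves, AUC and Youden's index follow, and the MID is the difference in mean change between improved and stable participants. Assessment mode is not mentioned in either part.

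**The concern.** A count made by a clinician in clinic, a count made over video, a count from still photographs and a count reported by the patient are four different measurements. If a participant is measured one way at baseline and another way at month 6, the difference contains a mode effect that no feature of the stated analysis removes.

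Two results are exposed. The first is the lesion-count change in each treatment group, which is meant to inform the workshop on future RCT designs. The second is the validation result. The abstract says the study is designed to validate instruments, and responsiveness and MID are secondary objectives. An AUC and MID from a mixture of modes belong to no single instrument that a later trial could adopt. Self-report adds a further difficulty, because the count and a patient-reported anchor then come from the same person.

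**Working it through.** The plan states no figure on this point, so there is none to reproduce. The check has two parts: reading the sections against each other, and an illustration on assumed values.

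**1. Can mode change within a participant?** Yes, by design.
- A patient not known to the recruiter has a face-to-face baseline and may have month 6 in clinic, by video, from photographs or by self-report. That is 1 × 4 = 4 possible pairs, 3 of them mixed.
- A patient already known may have any of the four modes at baseline and at month 6. That is 4 × 4 = 16 ordered pairs, 12 of them mixed.
- The first recruit (18 February 2020, Trial status) preceded the March 2020 lockdown that led to the remote options.

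**2. Does the stated analysis separate the pairs?** No. The change estimate is per outcome and group. The general confounder sentence could accommodate mode as a covariate for change, but it does not extend to the ROC/MID paragraph.

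**3. Size of a mode effect on mean change.** Let *s* be the share of participants moving from clinic to remote and *r* the ratio of remote to clinic counts. Neither is in the documents, so both are assumptions. Suppose there is no true change and participants who switch have the same average count as the others. Then

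apparent change in mean count = *s* × (*r* − 1).

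| *s* | *r* = 0.70 | *r* = 0.85 | *r* = 1.15 | *r* = 1.30 |
|---|---|---|---|---|
| 25% | −7.5% | −3.75% | +3.75% | +7.5% |
| 50% | −15% | −7.5% | +7.5% | +15% |
| 75% | −22.5% | −11.25% | +11.25% | +22.5% |

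For example, 0.50 × (0.70 − 1) = −0.15. Participants who go from a remote baseline to a clinic review contribute with the opposite sign, so switches in the two directions partly cancel.

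**4. AUC if a mode change adds only random error.** Assume the change score has SD 1 in both anchor groups, a true difference of 1 SD, and extra error of SD *k* in half of each group. Without the error, AUC = Φ(1/√2) = 0.76. With it, a random pair of one improved and one stable participant has variance 2, 2 + *k*² or 2 + 2*k*², with probabilities 0.25, 0.50 and 0.25.
- *k* = 0.5: 0.25 × 0.760 + 0.50 × 0.748 + 0.25 × 0.736 ≈ 0.75.
- *k* = 1.0: 0.25 × 0.760 + 0.50 × 0.718 + 0.25 × 0.691 ≈ 0.72.

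**5. MID.** If a mode change shifts the score by *b* SD, the MID shifts by *b* × (share switching among improved − share switching among stable). With 60% and 40% (assumed), *b* = 0.25 gives 0.25 × 0.20 = 0.05 SD, and *b* = 0.5 gives 0.10 SD. With equal shares the shift is zero.

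**6. Shared source.** The global assessment in the outcome list is the Patient Global Assessment, and the change-in-severity anchor question is also completed by the participant. When the lesion count is self-reported as well, count and anchor share a reporter. That can raise their agreement, and so the AUC, which is the opposite direction to step 4.

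**The case against.** The strongest reply is that this is a condensed article. The analysis plan, full protocol and case report forms are not shown, and they may record mode and adjust for it. That stands as a limit: it cannot be said that mode goes unrecorded. It does not dispose of the point, because the sections that are shown conflict in their description of the measurement, and the analyses they do state would, if followed as written, mix modes.

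A second reply is that being recorded by the clinician does not mean being examined in person, so the retention section merely explains where remote findings come from. That reading is possible for video and perhaps for photographs. It does not fit a self-reported count, which is not a clinical examination whoever enters it.

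A third reply is that the consequence is limited. This is correct. The study is a descriptive feasibility cohort without p values, the primary outcome is eligibility and willingness at baseline, and remote assessment was an openly declared pandemic adaptation from which the discussion hopes to learn. Step 4 shows only a modest loss of AUC, and step 5 shows no MID shift when switching is balanced.

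Finally, restricting the main change estimate to same-mode pairs could itself introduce selection, since those who attend in person need not resemble the rest. That is accepted, and it shapes the fix.

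**Conclusion.** The point holds as an inconsistency in how the lesion assessment is described, combined with an analysis that does not distinguish modes. It should be corrected, but it does not threaten the primary outcome or the patient-completed questionnaires. It affects lesion counts and other examined signs.

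Size and direction are unknown. The range of ±7.5% to ±22.5% is the extreme of the illustration for 25% to 75% switching and count ratios of 0.70 to 1.30; all of these values are assumed. For the AUC, random error pulls down and shared reporting can push up.

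A reader might infer three stronger things that the documents do not support:
- **That all counts will be analysed as one clinician measure.** No section says so. It is a reading of several sections together.
- **That remote assessment will produce a spurious improvement.** This needs remote undercounting and movement only from clinic to remote. Self-report could overcount, and a remote baseline is permitted.
- **That mode differs by treatment group because procedural patients attend more often in person.** No section reports mode by group, and follow-up reviews are stated not to be tied to treatment schedules.

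**What to change.** 1. Reconcile Follow-up data collection with the retention section, so that a self-reported count is not described as a repeated clinical examination. State who counts lesions from photographs.
2. Record the mode (clinic, video, photograph, self-report) at baseline and at every review, if this is not already done. For past reviews, complete it retrospectively where site records allow; the documents do not say whether they do.
3. Keep the all-participant lesion-count change estimate. Report it also by combination of baseline and 6-month mode, with a sensitivity analysis in same-mode pairs.
4. Base any AUC and MID presented for a clinician lesion count on pairs assessed in person by a clinician at both visits. Report self-report and the other combinations separately, and note the shared source with a patient-reported anchor.

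**Cost.** One data field and a few lines of analysis text. The price in information is fewer pairs, wider intervals and possible selection in the lesion-count validation set. With 150 participants and about 20 expected in the least favoured option (13% × 150 = 19.5), the breakdown by mode within single treatment groups will be thin and is best shown across all participants, with group tables as description only.

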### Data management

#### Data collection

Quantitative data will be captured electronically and stored within a custom-built SQL database developed within the CTR. Paper copies of CRFs are available if required. Paper CRFs will not be returned to the CTR except in the case of archiving Investigator Site Files.

Data collection can be undertaken by a suitably qualified and experienced clinician, (nurse, doctor or surgeon) employed at the recruiting NHS site.

Qualitative interviews with participants and clinicians will be undertaken by a member of the research team. Interviews will be recorded, transcribed verbatim and stored on a secure access restricted platform at the University of Nottingham.

Participants will be identified by a unique study identification number (PID).

#### Management of text message data

Text message responses from participants will be held in an Application Programming Interface (API) built by Esendex; a telecommunications service provider. A command from the THESEUS SQL database will retrieve the text message data and associated metadata from the Esendex API on a daily basis.

#### Data quality

During data entry validation checks will automatically occur, as validations have been written into the database system.

#### Security

Access to all data, whether paper or electronic, will be restricted to delegated site staff and researchers at the CTR.

#### Confidentiality

A data management plan was developed prior to recruitment commencing.

CTR and study site delegation logs will record who is permitted to enter data and access data held in the THESEUS database. Staff added to the site delegation log will have access to research data relating to participants at their site only. Training on data safety and security will be delivered to local investigators and staff prior to recruitment at site.

#### Personal and identifiable data

Personal and identifiable data about the participant is collected at site. Participant consent is taken at site on a paper form and will contain the participant’s name. Paper-based consent forms will be stored separately to any paper-based clinical data in a locked cabinet. All hard copies of participant data will be stored in locked cabinets.

The THESEUS registration form is an online form which is used to collect participant contact details among other data. Participant registration data are entered directly onto the THESEUS SQL database. This information will be restricted and can only be accessed by using a unique username and password.

#### Electronic data security

The THESEUS SQL database may be accessed remotely via a web interface. The database is held on a secure Cardiff University server and a secure login is required for access. Researchers at recruiting sites can use any device with an internet connection to add data to the database. Data will not be stored offline on any devices. If no internet connection is available, data collection will be done on paper and then transferred on to the database at a later date.

Participants’ mobile phone numbers for the pain score text messages are accessed automatically by Esendex from the participant registration form held in the THESEUS SQL database. The pain NRS score responses from the text messages are imported back into the THESEUS SQL database and linked to the participants’ unique PID. Both the THESEUS Esendex account and the Esendex API can only be accessed by using a unique username and password.

#### Transferring data securely

The CTR will receive a scanned copy of the consent form from the NHS sites participating in the study. Scanned copies of consent forms will be transferred to the THESEUS email account using Cardiff FastFile, a secure file transfer platform.

With participant consent, their contact details will be shared with qualitative researchers based at Nottingham University to enable participants from the main study to be contacted to take part in a qualitative interview. This data will be shared as and when it is needed using a password protected Excel spreadsheet and transferred using Cardiff FastFile.

### Statistical methods

#### Statistical methods for primary and secondary outcomes

We will describe the eligibility and recruitment of participants into the study, their willingness to use the different intervention options at baseline, and their final intervention choice alongside their reasons. The group membership of the final intervention choice will be described using summary statistics using data collected at baseline, (including demographics, clinical history, severity of HS) to determine the drivers of treatment choice. We will also examine patients’ willingness to receive each treatment and their ranking of the treatments, (participant preference), and the clinicians’ assessment of their eligibility. We will describe the number and characteristics of individuals not eligible for each treatment option to understand clinicians’ treatment choices and why individuals were not suitable, to inform a future trial’s eligibility criteria and target group.

Over the study period, we will report whether patients continue with and adhere to their chosen intervention or whether they switch to alternative HS interventions during the study period. Within an intervention option and where there is variation in fidelity, we will explore the characteristics of non-adherence. Where a patient switches intervention, we will report the reasons for this and explore the characteristics of individuals that switch, (including intervention type, skin sites and other baseline demographics). Rates of loss to follow-up over the study period will be reported.

Clinical outcomes will be described using proportions, mean, (SD) or median, (25th–75th centiles) at each time point. (baseline, 3 and 6 months). Effect over time, baseline to 6 months, will be estimated for each efficacy outcome for each group with 95% CIs. Potential confounders of outcome will be assessed using regression methods but as this study is a feasibility study and not powered to detect differences between arms, p values will not be presented. We will estimate the clustering of outcomes within recruitment sites using the intracluster correlation coefficient, (ICC) and compare this ICC estimate with estimates from other relevant large RCTs.

For validation of core outcome instruments, global assessment will be used as our anchor tool to allow estimation of the MID. This will be used to dichotomise outcomes into those with clinically meaningful change and those without clinically meaningful change, (stable or worse). Receiver operating characteristic curves will be generated, and the area under the curve calculated as a measure of the outcome’s ability to detect clinically relevant change. Youden’s J index will be used to determine the minimal important change, and the MID will be calculated as the difference between the mean change in the improved and stable subgroups.^17^

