**Methods and analysis:**

The THESEUS study is a prospective observational cohort study. Participants, adults with active HS of any severity, will be asked to select one of five HS treatment options that is appropriate for their HS care. Participants will be allocated to their chosen treatment intervention and followed for a period of up to 12 months. Outcomes will be assessed at 3-monthly intervals using HISTORIC core outcome instruments. Video recordings of the surgical and laser operations will provide informational and training videos for future trials. Nested mixed-methods studies will characterise the interventions in clinical practice, understand facilitators and barriers to recruitment into future HS RCTs and examine patients’ and clinicians’ perspectives on HS treatment choices.

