#### Intervention description

Our study design allows centres to offer standard care, where the clinician and patient feels this is most appropriate, as well as the opportunity to offer treatments that are less commonly used in the UK. Laser treatment and deroofing of skin tunnels are not standard treatments in the UK, but they are both included in the summary recommendations of the European HS guidelines.^12^ As the study is observational in design, normal National Health Service (NHS) waiting lists apply.

Participants can choose one of five treatment options, depending on their suitability as assessed by their clinician and on the availability of the options at each recruiting centre. Each site is required to provide at least four of the five interventions:

Oral doxycycline 200 mg one time per day for 6 months, with the option to continue for up to a further 6 months.Oral clindamycin and rifampicin both 300 mg two times per day as a combined course for 10 weeks, with the option to continue up to 6 months.Laser treatment using nd-YAG laser, (skin types 2–6) or alexandrite/diode laser, (skin types 1–3) administered on four occasions each 1 month apart.Deroofing of skin tunnels using electrocautery, (optimal protocol to be determined by UK experts and provided to centres as a training package including a video). It is expected that by following this training video, healthcare professionals including dermatologists and plastic surgeons will be able to perform the intervention. The procedure is carried out under local anaesthetic, repeated during the next 6 months if necessary. The total area treated at one time is limited by the volume of local anaesthetic needed and expected degree of impairment of activities of daily living during recovery. A training video was produced as part of the THESEUS study and so far has been viewed more than half a million times: https://www.youtube.com/watch?v=ftizgrBMzok.^13^Conventional surgery, (narrow or wide excision, with a range of closure methods depending on the preference of the clinician), with the option to receive another intervention or combination of interventions 6 months after the surgery and for up to a further 6 months.

Following the initial 6 months of the chosen intervention, participants have the choice to continue with the intervention or to switch to another intervention or combination of interventions.

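### Clinical outcomes are collected to month 12 but summarised only to month 6 from baseline, so a procedure delivered late has one review or none after treatment in the stated analysis

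*Protocol article*

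**What the plan says.** All places are in the protocol article.

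- **Collection.** The abstract states: "Outcomes will be assessed at 3-monthly intervals using HISTORIC core outcome instruments". Under Follow-up data collection, reviews take place "at 3 months, 6 months, 9 months and up to 12 months after the baseline appointment". On the examination, that section says: "The clinical examination will be repeated at each follow-up review and recorded by the clinician". The participant measures, with the anchor for change in severity added, "will be completed by the participant at each follow-up review". Table 1 agrees: the outcome instruments are marked at months 3, 6, 9 and 12.
- **Clock.** The same section says: "Follow-up reviews are not anchored to treatment schedules", and adds that reviews go ahead even if the intervention has not yet been received. The intervention description says that "normal National Health Service (NHS) waiting lists apply". The section on discontinuing or modifying interventions foresees a substantial delay for some options and allows another intervention during the wait.
- **Analysis.** The statistical methods section describes clinical outcomes "at each time point. (baseline, 3 and 6 months"). It continues: "Effect over time, baseline to 6 months, will be estimated for each efficacy outcome for each group with 95% CIs". The Outcomes section likewise places the efficacy estimates after 6 months of follow-up. No summary of clinical outcomes at 9 or 12 months is stated, and no reason is given for stopping at 6.
- **Instrument validation.** The paragraph on ROC curves, Youden's index and the minimum important difference (MID) names no time point.

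**The concern.** The analysis window and the treatment run on different clocks. The window closes six months after the baseline appointment, while treatment starts whenever the waiting list allows. For a drug started at baseline the two coincide. For surgery, deroofing or laser with a wait, part or all of the interval from baseline to 6 months comes before treatment.

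The per-group effect with its 95% CI would then average participants assessed after treatment with participants still waiting, and the result would be labelled as that group's change. According to the Outcomes section, these estimates are meant to inform the design of future trials. Change in a procedural group could be misjudged for a reason unrelated to the procedure, while later reviews that do follow treatment would stay out of the summary. The strengths and limitations box says that the pandemic hampered delivery of conventional surgery, so delay is a practical matter here.

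**Working it through.** The plan gives no figure to reproduce on this point. The check is a count of scheduled reviews.

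**Inputs**

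- Scheduled reviews after baseline: months 3, 6, 9 and 12 (Follow-up data collection, Table 1).
- Last review in the stated clinical-outcome analysis: month 6 (statistical methods).
- Month of the procedure, *d*, counted from baseline: not given, so it is varied.
- Laser course: four sessions one month apart, so three months from first to last (intervention description).

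**Share of reviews in the stated analysis.** Months 3 and 6 are used out of 3, 6, 9 and 12, that is 2 of 4. This counts scheduled reviews. Follow-up is only up to 12 months, so the share of actual records left out may be below half.

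**Reviews after a single procedure.** Count the reviews *t* with *t* > *d*, once with *t* ≤ 6 and once with *t* ≤ 12:

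| Procedure done | Reviews after it, analysis to month 6 | Reviews after it, collected to month 12 |
|---|---|---|
| before month 3 | 2 (months 3, 6) | 4 |
| month 3 to before month 6 | 1 (month 6) | 3 (months 6, 9, 12) |
| month 6 to before month 9 | 0 | 2 (months 9, 12) |
| month 9 to before month 12 | 0 | 1 (month 12) |

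A single review after treatment can also come soon after it: for a procedure at month 5, the month-6 review is 6 − 5 = 1 month later.

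**Laser, counted from the last session.** The course ends at *d* + 3. With a start at month 3 it ends at month 6, so no review up to month 6 follows the last session, but months 9 and 12 do. Any later start also leaves none up to month 6.

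**Does the switching rule explain the cut-off?** The intervention description counts the switching period from treatment: after the first six months of the chosen intervention or, for conventional surgery, six months after the operation. Take surgery at month 4. Six months later is month 4 + 6 = 10. The reviews at months 6 and 9 both fall inside that period, yet the stated analysis uses only month 6. The cut-off therefore does not match the switching rule once treatment is delayed.

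**The case against.** The best defence is that six months is a consistent choice. The Outcomes section defines efficacy after 6 months of follow-up, the methods section analyses exactly that, and participants are asked to stay on their choice for six months before switching freely. Later reviews mix treatments. The study is a feasibility cohort with a primary outcome measured at baseline, and no p values are planned for efficacy. Further descriptive tables could also sit in a full protocol or analysis plan that is not shown.

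Much of this stands. Six months is a reasonable main horizon, and the primary outcome is unaffected. But the article does more than leave later summaries unmentioned: it spells out which time points are meant. The switching argument also fails for delayed treatment, as shown above. Daily pain texts do run for up to 12 weeks from the start of the intervention, but they cover pain only.

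Three stronger readings are tempting, and the documents support none of them.

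- *Instrument validation loses half of its change scores.* The validation paragraph sets no time point. The Outcomes section says only that the 6-month estimates contribute to validation, which is not a limit. Any figure for lost information would rest on an inferred restriction and assumed correlations.
- *The later questionnaires are never used.* Months 9 and 12 feed loss to follow-up over 12 months and the reporting of switching and adherence over the study period. They may also feed validation.
- *The surgical groups would be described mainly before treatment.* No waiting times are given, and a statement that delivery was hampered does not show how many procedures fell after month 3 or month 6.

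**Conclusion.** The point holds as a mismatch between a stated analysis window and a follow-up clock that ignores the start of treatment. The clinical-outcome summary covers two of the four scheduled reviews after baseline. It leaves one review after a procedure done from month 3 to before month 6, and none after one done at or after month 6, although up to three and up to two respectively are collected. These counts assume that reviews occur at their planned months and that follow-up reaches month 12. The number of participants affected is unknown. It would be zero if every procedure were done before month 3, and it grows with the length of the waits. The consequence is confined to secondary, descriptive efficacy estimates, mostly in the procedural groups. It deserves correction because those estimates are meant to guide later trials and the data needed are already being collected.

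**What to change.** 1. In the statistical methods section, keep baseline to 6 months as the main group summary, and extend the descriptive time points to 9 and 12 months. Label the later ones as descriptive and show them by treatment received to date.
2. Add summaries by time since the intervention was delivered, so that effect in the procedural groups is not estimated from reviews made before treatment. Treatments and procedures received are recorded at each review, and the pain texts are timed from the start of the intervention, so the timing should be available.
3. In the validation paragraph, state which reviews enter the ROC and MID analyses. If several reviews per participant are pooled, allow for clustering within participant, for example by bootstrapping participants.

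The cost is a few changed sentences and some extra descriptive tables, with no new visits, data or sample-size change. The downside is small: later reviews mix treatments after permitted switching and may be less complete, which the labelling should make plain.
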